### ***Country and region-specific analysis***

Additional questions may be looked at following this first phase and might include country-specific questions in order to increase the relevance of HIV prevention, care and treatment interventions, zero discrimination interventions and advocacy, or human rights interventions, among others.

### ***Feedbacks of results to communities***

Dashboards on key survey indicators will be prepared at country level and posted on the [Key Population Atlas](#) web-site and on the [LGBT Foundation](#) web-site.

Results and key findings for countries and regions will be prepared in English and made available to LGBTI communities at country, regional and global levels.

Advocacy material will also be prepared by UNAIDS, the LGBTI Foundation and their partners, aiming at promotion of a more inclusive environment for LGBTI, zero discrimination campaign, “Know your status” campaign for HIV prevention, International day against homophobia (IDAHO) and others.

#### b) Relevance of the research to the health needs of the target population

The number of new HIV infections is decreasing worldwide but incidence is still increasing among the transgender people as well as among the gay and other men having sex with men[20]. Some surveys[14, 21], essentially in high-income countries, suggest that stigma, discrimination, homophobia are associated with poorer mental health and riskier behaviour in terms of vulnerability to HIV infection but data is lacking to study the level of this relationship in low- and middle-income countries and prohibit analysis across countries.

This research is relevant as it aims to fill this information gap in low- and middle-income countries. Findings can be used by partners, LGBTI civil society organisations and UNAIDS country offices for advocacy for more LGBTI-inclusive public health programs.

Furthermore, the survey can provide additional added value thanks to the econometric analysis of socioecological variables together with behavioural variables. To the best of our knowledge, this is the first time such a multi-country data collection on lesbian, gay, bisexual, transgender and intersex people and analysis will be performed. If demonstrated, findings could help addressing socioeconomic inequalities correlated with increased vulnerability to HIV and STI infections.

To our knowledge, this is the first survey provided the scope, focus, and sampling design. Repeated every year this cross-sectional survey could provide useful information on the changing patterns across variables and monitor trends in exposures and outcomes in LGBTI communities. Thus, this study can become a baseline for future research. This study is sought to provide information for public health planning, monitoring, and evaluation at country, regional and global levels.

#### c) Sampling strategy, recruitment and voluntary informed consent

The target population of the survey are 18+ year-old LGBTI people. The survey can be accessed using a web [link](#) that will be provided at LGBTI social networks, e.g. the LGBT Foundation social networks, as well as national and regional LGBTI community networks. The survey will be opened for a duration of 3 months. Recruitment will not involve any direct recruitment and is anonymized. Participation in the survey is not incentivised. We are aware of the limitations associated to these voluntary recruitment channels and we are exploring, with LGBTI civil society organisations and UNAIDS teams at country and regional levels, all additional opportunities that could increase the participation of marginalised or remote communities and individuals.

It was considered that participants who are afraid to share information about risk behaviours or HIV status may drop out of the survey or falsify their responses. To successfully survey LGBTI people, these biases are being minimized by obtaining fully informed voluntary consent at the start of the survey from participants and ensuring their absolute confidentiality.

The informed consent of voluntary participants is summarised at the introduction of the survey and the following information is provided through a link:

- a concise description of the survey and the organization conducting it, the survey objectives, the populations being invited to participate;
- a clear indication that participation is voluntary and that participants have the right of withdrawal from the survey at any time, or skip any sensitive question/s;
- a description of the participant's role in the survey, including duration of participation, the general nature of the questions;
- a description of the possible discomforts of participation;
- a description of the benefits to the community that are expected to come from the survey
- a description of how the findings will be made available to the respondents and the LGBTI community
- measures made to protect the privacy and confidentiality of the participant and any information that the person provides;
- documentation that the protocol was reviewed and approved by Research Ethics Review Committee (*to be completed once WHO ERC approval*);
- how the results of the survey will be used. This includes explicitly the possible use of the data for scholar purpose, such as doctoral or post-doctoral productions by the research team
- contact information and procedures for contacting the investigators in case of further queries and/or questions.

Only 18+ year-old participants can participate in the survey provided an informed consent. Participants are required to acknowledge their informed consent to enter the survey by clicking on the "OK" button (question 1, mandatory).

#### d) Justification of the research design

Worldwide, LGBTI people contend with exceptionally high risks for HIV infection, stigma and discrimination, and for exclusion from HIV and other health services. LGBTI people are often hidden and difficult to assess as part of general population-based surveys. Thus, assessing their exposures and outcomes and burden of HIV disease is extremely challenging and necessary. This presents a dilemma for HIV surveillance as their omission from surveillance systems leaves significant gaps in our understanding of HIV epidemics. We aim to fulfil the knowledge and apply web-based community surveying to protect person's privacy and ensure data confidentiality during and after the survey.

#### e) Gender considerations relevant to the project

The online survey is about people with various sexual orientation and gender identities. We made sure the gender diversity is acknowledged and adequately reflected in the survey.

The survey was provided for review to the members of the LGBTI community with various sexual orientation and gender identities. Their feedback and comments were considered and analysed at various stages of proposal development. The comments were considered and incorporated it the final version of the questionnaire.

#### f) The benefits that the research will likely produce

To research participants and the LGBTI community

To applied scientific knowledge

The main benefit of the online survey is to inform how the quality of life, stigma -both perceived and enacted-, the discrimination, the social status, the economic vulnerabilities the Lesbian, Gay, Bisexual, Transgender and Intersex People (LGBTI) living in low- and middle-income countries are facing is associated with their vulnerability to HIV infection and to their health status.

The analysis that will follow will support advocacy for more inclusive society and better programme design for LGBTI people in low- and middle-income countries.

#### g) A description of physical, social, psychological and economic risks to both individuals and communities

The safety and data security of the target population is a top priority in planning and implementation of our survey. We learned from the experience of the previous web-based surveys (e.g. EMIS, etc.), and consulted with the community-based organizations, including the LGBT Foundation. The survey will be conducted anonymously, meaning that personal identifiers will not be recorded on any forms. Unique survey codes will be used in all records and constructed without the use of personal identifying information such as any identifiable numbers.

By design this survey is a cross-sectional survey, where the investigators will measure the outcome and the exposures not altering the exposure status.

The survey instruments were previously administrated in communities and proved minimal to no psychological risk for the respondents. We still acknowledge that some sensitive personal questions may trigger anxiety in some respondents. This can be the case with the following questions and/or statements:

- When was your last HIV test?
- Do you know your HIV status?
- Thinking about your last anal sex partner without any kind of HIV prevention method (that is without condom, PrEP or an undetectable viral load), did you know his HIV status?
- I feel comfortable being sexually attracted to other men.
- I have lost friends by telling them I have HIV.
- The questions of the patient health questionnaire on anxiety and depression (PHQ-4).

However, we anticipate minimal to no risk for the study participants. To monitor any related cases, we created a mailbox to respond quickly and appropriately on any query and/or event related to this survey.

#### h) Vulnerability to harm or to risk of exploitation

The survey does not imply any person-to-person contact. It does not collect any personal information and records are unidentifiable. The questions, taken all together, do not reveal any information that could make respondents vulnerable to harm or to risk of exploitation. The questionnaire does not use or collect geolocation data, it does not install any tracker cookies on the device of the respondents. We anticipate no harm or risk of exploitation.

#### i) Steps that will be taken to minimise the risks to participants, including confidentiality and privacy

As described in the section above, the online questionnaire should not entail no more than minimal risk in terms of potential stress and/or anxiety while responding to the questionnaire. The online

questionnaire compiles questions previously used in other surveys and, to the best of our knowledge, do not have any physical risk.

The data privacy and protection of information obtained from participants is important for this survey. To protect the anonymity and data privacy of the participants, the following steps have been taken:

- The study is made available to LGBTI population through a secure, SSL encrypted connection link
- The link does not require any personal identifier, email, phone or person-to-person contact
- Data in transit (ex: while responding online) are encrypted using secure TLS cryptographic protocols
- The collection tool, Survey Monkey, has [certified its compliance](#) with the EU-U.S. Privacy Shield Framework (GDPR) and Swiss-U.S. Privacy Shield
- The questionnaire does not collect any personal information. Questions, even taken all together, do not reveal any information that could enable to identify the respondents or his/her geolocation
- The collection tool does not install any targeting or advertising cookies
- IP addresses are instantly decoupled from the questionnaire, encrypted and deleted at the end of the online survey (3 months) by the survey tool
- Data records are unidentifiable

We have, to the best of our knowledge, taken all the measures to prevent any identification of the respondents by the research team as well as by any authority.

We believe we have taken all the necessary steps to ensure data privacy and to protect the confidentiality of information obtained from participants, and to protect them from social or economic discrimination or stigmatization following their participation to the online questionnaire.

Furthermore, as mentioned above, a mailbox representing the participating agencies will be provided to address any query and/or event related to this survey.

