### Rationale for the research

Behavioural surveillance among LGBTI populations is a priority in all epidemic settings. HIV control efforts directed at high-risk populations can have a substantial impact on the epidemic. HIV policies and programmes will be more effective if they are informed by measures of HIV prevalence among those populations, trends in their HIV-related risk behaviours, and the extent to which they access HIV and other health related services. This makes this survey a critical undertaking for monitoring the HIV epidemic and evaluating HIV control efforts.

Policies that criminalize behaviours of high-risk populations or limit their access to HIV and other health related services may further elevate their risk of acquiring and transmitting HIV. The infringement of human rights, verbal and physical violence and denial of health services associated with stigma and discrimination based on sexual orientation and gender identity is a demonstrated public health issue. Stigma is a central driver of morbidity and mortality at a population level[1]. Communities facing enacted sexual stigma are more likely to engage in sexual risk behaviours[2, 3]. They are less likely to adhere to their antiretroviral treatment[4] and have lower HIV testing rates[4-10]. Internalized homonegativity is associated with lower levels of HIV testing and lower levels of condom use[11]. A socio-ecological approach to health-related behaviour[12] allows for studies of the role of stigma related to sexual orientation and gender identity in their broader structural and social dimensions[1, 13, 14]. Most studies of homophobia have focused on the individual level. Being able to identify the level of homophobia at country level is important to guide public health policies as recent evidence shows that reductions in the homophobic climate are associated with improved health outcomes[15]. Data related to structural factors, such as the existence of legislation against LGBTI human rights, are generally available, although unevenly among low- and middle-income countries. But there is a lack of individual and interpersonal data on members of the LGBTI community in low- and middle-income countries.

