#### p) Limitations of the survey

This survey will be performed online. This channel is a demonstrated channel enabling higher number of respondents among hard-to-reach populations, faster recruitment, lower operational cost, and greater level of anonymity provided to participants. There are nevertheless limitations that should be acknowledged.

First is the statistical representativity of the survey. There is a selection bias in using social media and social networks. We will apply available techniques to correct for the bias that results from differential access to, and use of, the internet. Like other surveillance for key populations, the survey does not aim of a nationally representative sample of the LGBTI population of a said country.

Second is the access to the internet. Some members of the LGBTI community in low- and middle-income countries may face financial or material constraints to access the internet and thus the survey. UNAIDS Country teams will share the link of the survey with local LGBTI networks, encouraging them to see how they can facilitate an internet access to participants from their community, but it should be acknowledged that members of the LGBTI groups might not be represented.

The third limitation relates to the possible variations between languages. When available, we used validated translations of questions. When translations were not available, we made sure the translations were as close as possible from the original English version. This was achieved by performing translation and retranslation to English as proofreading. Despite of that, the specificities of the different languages make it almost impossible to ensure an exact correspondence. For

example, languages such as Japanese are highly contextual and situational and will thus require more words to describe “being comfortable”.

Finally, due to anonymity, self-reported responses such as country of residence or age cannot be verified by other means. In addition to the informed consent, the question on the age includes the choice “under 18”. Respondents selecting this answer will be considered as non-qualifiers.

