**(Thank you message)**

*Thank you very much for your support.*

*Sign up to get the results of this study and participate in future studies, your information is completely anonymous, any IP address is decoupled, encrypted and deleted at the end of the study. [https://lgbt-token.org/research\\_signup](https://lgbt-token.org/research_signup) You may share the survey via: <https://www.research.net/r/LGBTHappinessResearch>*

*Get tested for HIV regularly. For more information: <https://hornet.com/about/know-your-status/>*

(Only participant who answered I'm HIV positive are offered to participate to module 3 below)

exit

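### The assurance that all measures against identification have been taken is wider than the eight listed steps, none of which deals with a survey address containing LGBT staying in the browser or being seen on a device

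*Protocol*

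**What the plan says.** Section i) lists eight steps that protect anonymity and data privacy. Two examples are "Data in transit (ex: while responding online) are encrypted using secure TLS cryptographic protocols" and "IP addresses are instantly decoupled from the questionnaire, encrypted and deleted at the end of the online survey (3 months) by the survey tool".

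Two assurances follow the list. The first, given to the best of the team's knowledge, is that it has "taken all the measures to prevent any identification of the respondents by the research team as well as by any authority". The second begins "We believe we have taken all the necessary steps to ensure data privacy" and goes on to cover discrimination or stigmatisation that might follow from taking part. Section h) adds that the questionnaire places no tracker cookies on respondents' devices and that the team expects neither harm nor exploitation.

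The thank-you message in Appendix 1 gives a public address for passing the survey on, with the path "LGBTHappinessResearch". Section p) says that UNAIDS country teams will send the link to local LGBTI networks, "encouraging them to see how they can facilitate an internet access to participants from their community". The survey objectives in section a) set no geographical limit. The rationale refers to "Policies that criminalize behaviours of high-risk populations" and to verbal and physical violence linked to sexual orientation and gender identity.

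**The concern.** The listed steps follow the data from the respondent's connection to the stored record. They do not consider the place where the survey is filled in. A browser normally keeps the addresses it has opened, and this address names the community being surveyed. Someone who looks at the phone or computer, whether a relative, an employer or an official, could see that the page was opened without touching the connection, the survey tool or the dataset.

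Two things are at stake. The first is safety: in a hostile setting, a visit to a page labelled LGBT may be enough to raise suspicion. The second is the quality of the data. Section c) accepts that frightened participants may drop out or answer falsely, and relies on confidentiality to limit this. If the fear is greatest where the climate is most hostile, the effect would fall on the settings that matter most for the research question on homophobic climate. The documents contain nothing that would let this second effect be estimated.

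**Working it through.** No figure in the protocol bears on this point, so the check is a comparison of texts.

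**Step 1. Sort the eight steps in section i) by what they protect.**

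| What is protected | Steps | Count |
|---|---|---|
| Connection | SSL link; TLS in transit | 2 |
| Survey tool and stored records | Privacy Shield certification; handling and deletion of IP addresses; unidentifiable records | 3 |
| Information asked for | No identifier needed to enter; no personal information in the questions | 2 |
| Device | No targeting or advertising cookies | 1 |

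The total is 2 + 3 + 2 + 1 = 8.

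**Step 2. Ask which steps deal with the address remaining in the browser or being seen on a screen.** TLS hides the address path while it travels, but not in the browser's own history. The cookie step does concern the device, but it does not remove the address. The result is 0 of 8.

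**Step 3. Look for cover elsewhere in the protocol.** The exit button in Appendix 1 is described only as a way to leave the survey, and section l) treats its use as exclusion. The closing text, which can be read in full, says nothing about browser history or private browsing. Section c) describes a linked text at the start that covers privacy measures, but that text cannot be read here.

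**Step 4. Set the assurances beside this result.** An authority that inspects a device falls within the first assurance in section i), which names any authority. A relative or employer falls outside that sentence, but within the second assurance on discrimination and stigmatisation and within the no-harm statement in section h). The list supports neither assurance for this route.

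**Step 5. Check whether the route is foreseeable from the protocol alone.** The address is in its appendix, the worldwide scope is in its objectives, and the hostile settings are in its rationale. It is.

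**The case against.** The case on the other side is substantial, and much of it stands.

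- **The assurances are qualified.** One is given to the best of the team's knowledge and the other as a belief. The sentence should not be read as an absolute guarantee. The qualifier does not, however, account for a risk that is visible in the protocol's own appendix.
- **The steps reach beyond the connection and the server.** A reader might infer that they stop there. They do not: two limit what is asked and one concerns cookies on the device.
- **Shared access is not stated.** A reader might take section p) to encourage shared computers. It speaks only of facilitating access in answer to financial or material constraints, and data credit or funds would fit equally well. Shared devices are possible, no more.
- **The external links on the closing page are not part of the problem.** Displaying a link leaves no trace of its target. Only following it does, and that is already the respondent's choice.
- **The LGBT address appears as a link for sharing.** That it is also the main entry address is likely, but is inferred, because section c) does not show its link target. Anyone who receives the shared link would still enter by it.
- **The consent text is not available.** It may already carry advice on device privacy, so such advice cannot be called absent from the survey. If it is there, the address and the breadth of the assurances remain.
- **No two passages contradict each other.** This is correct. The point is an assurance wider than its support, together with an inexpensive remedy.

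**Conclusion.** The point holds in a limited form. Sections h) and i) give assurances that the eight listed steps do not fully support, because none of the eight deals with a survey address containing LGBT being kept or seen on the respondent's device. Given the worldwide scope and the hostile settings that the rationale cites, this is a foreseeable risk that can be reduced at little cost.

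A reader might infer that participation can be read from the device. The documents do not support that. A stored address shows that a page was opened. It does not show that the survey was completed, what was answered or, on a computer used by several people, who opened it. How long the trace lasts depends on device settings that the protocol does not describe.

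The size cannot be put as a proportion of respondents, since the documents say nothing about device use or inspection. The conclusion rests on two assumptions: that the address in the thank-you message is one by which respondents enter, and that ordinary browsers keep a history unless told otherwise.

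**What to change.** 1. **Address.** Use a neutral survey address with no LGBT or HIV term, both for promotion and in the sharing line of the thank-you message. This matters most, because any advice on the consent page is read only after the address has been opened.
2. **Device privacy.** Add one line to the closing page, and to the consent page if it is not already there, for example: *If other people can see this device, use a private window, close it when you finish and clear the browsing history.*
3. **Assurances.** Narrow the statements in sections h) and i) to the risks that the listed steps cover, and say plainly that a visit to the page may remain visible on the respondent's own device.

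The external links on the closing page can stay where they are.

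The cost is small. The address becomes slightly less recognisable in promotion. The protocol lists 17 languages including English, so one or two sentences in the other 16 come to 16 to 32 sentences for translation and back-translation. Nothing in the questionnaire content, sample size or analysis changes.
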